### Missing data

Predictive model-based multiple imputation will be used to impute missing data. Since the primary longitudinal models are a mixed linear regression, using a predictive model-based approach will allow for the use of more actual data to impute the missing data. The rate of missing data over time will be examined to determine if treatment, baseline weight, gender, age, and/or school are related to the missing data. If none of these factors is related to the missing data, it might be safe to assume data are missing completely at random.

### Sample size/power

The primary aim of this study is to compare change in academic achievement (comprehensive score) between the two treatments (A + PAAC vs. control). Power calculations were based on results from a secondary analysis of change in academic achievement from the completed PAAC study [10,11]. Since this is a cluster randomized design or an inherent ICC within the schools was assumed. The primary analysis will be conducted using a modified two-sample *t*-test [41] using a type I error rate of 5%. Table 3 describes the power for a range of ICCs, number of schools per treatment, and sample sizes within each school assuming an expected improvement in academic achievement of 5 points in the A + PAAC group, no change in the control group with a common standard deviation of 9 points, similar to results from the PAAC study [10].

**Table 3 T3:** Statistical power

**Schools per treatment**	**Students per school**	**Intra-Class correlation**					
		**0**	**0.01**	**0.03**	**0.05**	**0.07**	**0.1**
6	20	0.99	0.98	0.93	0.87	0.8	0.71
6	30	0.99	0.99	0.97	0.92	0.86	0.76
7	20	0.99	0.99	0.96	0.91	0.86	0.78
7	30	0.99	0.99	0.99	0.95	0.9	0.82

An ICC in the range of 0.03 to 0.07 is anticipated for academic achievement, thus to ensure at least 85% power for this confirmatory study, 17 schools were randomized between the two treatment groups with 40 students being recruited per school. Based on the power analysis above, power will be sufficient with as few as 20 students per school and ICCs as high as 0.10. Given the limited preliminary data, exact power calculations are not possible for the secondary endpoints. However, assuming a type I error rate of 5%, secondary endpoints have the following power: 0.99, 0.99, 0.96, 0.91, 0.84 and 0.74, to detect an effect size of 0.5 standard deviations for ICCs equal to 0, 0.01, 0.03, 0.05, 0.07 and 0.10, respectively. Thus, the study will have sufficient power to detect any clinically meaningful difference on the secondary endpoints.

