**Methods/design:**

Seventeen elementary schools were cluster randomized to A + PAAC or control for a 3-year trial. Classroom teachers were trained to deliver academic instruction through moderate-to-vigorous physical activity with a target of 100+ minutes of A + PAAC activities per week. The primary outcome measure is academic achievement measured by the Weschler Individual Achievement Test-III, which was administered at baseline (Fall 2011) and will be repeated in the spring of each year by assessors blinded to condition. Potential mediators of any association between A + PAAC and academic achievement will be examined on the same schedule and include changes in cognitive function, cardiovascular fitness, daily physical activity, BMI, and attention-to-task. An extensive process analysis will be conducted to document the fidelity of the intervention. School and student recruitment/randomization, teacher training, and baseline testing for A + PAAC have been completed. Nine schools were randomized to the intervention and 8 to control. A random sample of students in each school, stratified by gender and grade (A + PAAC = 370, Control = 317), was selected for outcome assessments from those who provided parental consent/child assent. Baseline data by intervention group are presented.

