## Results

### Analysis plan-primary aim: academic achievement

Changes (year 3 minus baseline) in academic achievement (WIAT-III comprehensive score) will be compared between students attending A + PAAC intervention and control schools using a modified two-sample *t*-test adjusted for the intra-class correlation (ICC) [41] with a type I error rate of 5%. Similar analysis will be completed for WIAT-III sub-scales and for each of the secondary endpoints (Kansas State Assessment, cognitive function, BMI, cardiovascular fitness, attention-to-task, daily physical activity). This longitudinal study will provide multiple assessments over time; therefore linear mixed models will be used to assess differences in between A + PAAC and control in the primary and secondary endpoints. A compound symmetric correlation structure for estimating the intraclass correlation coefficient (ICC) within a school is assumed.

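### Table 3 uses a normal or student-level reference distribution although schools are randomised, so its power figures are about 2 to 8 points too high at the anticipated ICCs; the 17-school design still meets its target

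*Protocol article*

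**What the plan says.** Schools are the unit of randomisation: "Nine schools were randomized to the intervention and 8 to control" (Abstract, Methods/design). The primary analysis compares changes by a two-sample t-test "adjusted for the intra-class correlation (ICC) [41] with a type I error rate of 5" per cent (Analysis plan, primary aim). Sample size/power names the same test, again "using a type I error rate of 5" per cent. Neither section states its degrees of freedom or reference distribution.

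The power inputs are "assuming an expected improvement in academic achievement of 5 points in the A + PAAC group" and "no change in the control group with a common standard deviation of 9 points". The article says "Table 3 describes the power for a range of ICCs, number of schools per treatment, and sample sizes within each school"; the table covers 6 or 7 schools per treatment, 20 or 30 students per school and ICCs from 0 to 0.10.

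The text then says "An ICC in the range of 0.03 to 0.07 is anticipated for academic achievement" and that, to secure at least 85% power, "17 schools were randomized between the two treatment groups with 40 students being recruited per school". It adds that 20 students per school would be enough even at an ICC of 0.10. For secondary endpoints it gives powers of 0.99, 0.99, 0.96, 0.91, 0.84 and 0.74 for an effect of 0.5 SD over the same six ICCs.

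**The concern.** A design effect inflates the variance of the treatment difference for clustering. It does not restore the information about that variance. With 12, 14 or 17 schools, the between-school variance is estimated from 12, 14 or 17 units, so the standardised difference should be referred to a t distribution on the number of schools minus 2: 10, 12 or 15 df. Using the normal distribution, or a t with several hundred student-level df, treats the variance as practically known.

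Two things are at stake. The printed powers would be too high, together with any conclusion that leans on them. And if the same reference distribution were carried into the primary test, the test would reject too often and its confidence intervals would be too narrow.

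**Working it through.** **Inputs** (all from Sample size/power unless noted): difference 5 points; SD of change 9; alpha 0.05; k schools per arm and m students per school as in Table 3; 9 versus 8 schools from the Abstract. Sidedness is not stated. Two-sided is used because it reproduces the table, while a one-sided normal formula misses by up to 10 points. School sizes are taken as equal; Table 2 gives 370 + 317 = 687 students, and 687/17 is about 40.

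**Formula.** SE = 9 × sqrt{[1 + (m − 1) × ICC]/m × (1/k1 + 1/k2)}, noncentrality = 5/SE. Power is then computed from (a) the normal distribution, (b) noncentral t on 2km − 2 student df, and (c) noncentral t on 2k − 2 school df.

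**Reproducing Table 3.** (a) and (b) each match all 24 cells within 0.01 and cannot be told apart at the printed precision. (c) does not match.

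| Schools × students | ICC | Stated | Normal | School df | Stated minus school df (points) |
|---|---|---|---|---|---|
| 6 × 20 | 0.03 | 0.93 | 0.930 | 0.871 | 5.9 |
| | 0.05 | 0.87 | 0.869 | 0.793 | 7.7 |
| | 0.07 | 0.80 | 0.805 | 0.720 | 8.0 |
| | 0.10 | 0.71 | 0.715 | 0.626 | 8.4 |
| 6 × 30 | 0.03 | 0.97 | 0.971 | 0.934 | 3.6 |
| | 0.05 | 0.92 | 0.920 | 0.858 | 6.2 |
| | 0.07 | 0.86 | 0.857 | 0.779 | 8.1 |
| | 0.10 | 0.76 | 0.761 | 0.673 | 8.7 |
| 7 × 20 | 0.03 | 0.96 | 0.960 | 0.925 | 3.5 |
| | 0.05 | 0.91 | 0.914 | 0.863 | 4.7 |
| | 0.07 | 0.86 | 0.861 | 0.798 | 6.2 |
| | 0.10 | 0.78 | 0.779 | 0.708 | 7.2 |
| 7 × 30 | 0.03 | 0.99 | 0.986 | 0.968 | 2.2 |
| | 0.05 | 0.95 | 0.953 | 0.915 | 3.5 |
| | 0.07 | 0.90 | 0.905 | 0.851 | 4.9 |
| | 0.10 | 0.82 | 0.822 | 0.754 | 6.6 |

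Worked cell, 6 × 30 at ICC 0.10: design effect 1 + 29 × 0.10 = 3.9; SE = 9 × sqrt(3.9/30 × 2/6) = 1.873; noncentrality 5/1.873 = 2.669. The normal distribution gives 0.761; t on 10 df (critical value 2.228) gives 0.673.

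**Secondary endpoints.** The design behind these powers is not named. With the difference set to 0.5 SD, the normal formula for 7 × 30 gives 0.999, 0.995, 0.963, 0.905, 0.837 and 0.737. That fits the printed series within 0.01. On 12 df the values are 0.997, 0.985, 0.930, 0.851, 0.771 and 0.664.

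**The design actually randomised**, 9 versus 8 schools, 15 df:

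| Students per school | Reference | ICC 0.03 | 0.05 | 0.07 | 0.10 |
|---|---|---|---|---|---|
| 40 | Normal | 0.998 | 0.988 | 0.963 | 0.904 |
| 40 | 15 df | 0.996 | 0.975 | 0.938 | 0.863 |
| 20 | Normal | 0.983 | 0.956 | 0.918 | 0.851 |
| 20 | 15 df | 0.968 | 0.928 | 0.879 | 0.801 |

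For 20 students at ICC 0.10: design effect 2.9, SE = 9 × sqrt(2.9/20 × (1/9 + 1/8)) = 1.665, noncentrality 3.00.

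**Type I error if the primary test used the same reference.** 2 × P(T on 15 df > 1.96) = 6.9%. In a simulation of 9 versus 8 schools of 40, with the ICC estimated by analysis of variance and set to zero when negative (200,000 trials per setting), normal or student-level critical values gave 6.7% to 7.0% at ICC 0.03 to 0.10. They gave 5.9% at ICC 0.01 (5.8% with student-level df) and 4.0% at ICC 0. With 15 df the size was 4.9% to 5.1% at ICC 0.03 to 0.10. The critical values are 1.96 and 2.13, so intervals would be about 8% too narrow.

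**The case against.** A reader might infer that the trial is underpowered. The documents do not support that. Table 3 stops at 7 schools per arm, whereas 17 schools were randomised. On 15 df the actual design exceeds 85% throughout the anticipated ICC range with 40 students per school, and also with 20. If two further df were lost to district strata (an assumption; the number of districts is not given), 40 students at ICC 0.10 would still give 0.855. For the actual design the overstatement is at most 2.5 points at ICC 0.03 to 0.07, and the 8.7-point gap lies outside both the anticipated ICC range and the randomised number of schools. This objection stands.

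A reader might also infer that the primary test will run at 7%. That is not shown either. The df are not stated, the cited method is not at hand, and a normal approximation used for planning does not fix the critical value used in the analysis. Small-sample df for the mixed models are commonly left to the analysis plan, so their absence is no fault here.

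Finally, the article does not define what power it regards as sufficient at ICC 0.10, and it attaches the 85% target to ICC 0.03 to 0.07. That softens the criticism of the 20-student statement but does not remove it. The statement rests on Table 3, whose own 20-student cells at ICC 0.10 are 0.71 and 0.78. Even for 17 schools it reaches 85% only on the normal formula.

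**Conclusion.** The point holds as an error in printed power figures. Table 3 overstates power by about 2 to 8 points at ICC 0.03 to 0.07 and by up to 8.7 points at ICC 0.10. The secondary-endpoint powers share the flaw: 0.96, 0.91, 0.84 and 0.74 become 0.93, 0.85, 0.77 and 0.66 at ICC 0.03, 0.05, 0.07 and 0.10, if the 7 × 30 design is the one behind them. The statement about 20 students at ICC 0.10 does not meet 85%: 0.63 and 0.71 for the tabulated rows, 0.80 for the 17 schools.

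The choice of 17 schools with 40 students is unaffected. The type I error figure of about 7% is conditional on the primary test using the same reference distribution, and it shrinks or disappears as the true ICC approaches zero if negative ICC estimates are set to zero. The results rest on two-sided testing, equal school sizes and an ICC estimated from the trial's own schools. This should be fixed, but it does not threaten the design.

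**What to change.** Recompute Table 3 and the secondary-endpoint powers for 9 versus 8 schools on school-level df, naming the design used. Correct the statement that 20 students per school suffice at ICC 0.10. State in the primary analysis section that the ICC-adjusted t-test is referred to t on 15 df (fewer if district enters the model), or that school means are analysed instead.

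The cost is a recomputed table and a few sentences. Stated power will be slightly lower than the normal formula gives for the same design (0.938 instead of 0.963 at ICC 0.07 with 40 students), and intervals slightly wider than with 1.96. No schools or students need to be added. Fixing the df before outcome analysis also settles how a test statistic between 1.96 and 2.13 would be read.

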## Discussion

Cross-sectional studies suggest an association between physical activity and academic achievement in elementary school children [1,2]. However, results from the few available prospective studies on this topic are mixed [3-6]. The available studies have primarily evaluated the effect of increased PE which, in elementary school, is generally restricted to 30 minutes/day, 2 or 3 days/week, and provides limited time in MVPA. Thus, if physical activity is to be increased in elementary schools, venues other than PE need to be developed and evaluated.

Promoting increased physical activity using A + PAAC has a number of potential advantages. The elementary school setting provides an opportunity to increase the levels of physical activity in a large population of children. A + PAAC alters the classroom environment such that children are not required to make an overt choice to be more physically active, but do so as part of the academic curriculum. Therefore, the probability that children will actually engage in increased physical activity is likely higher than other approaches where participation is volitional (i.e., sports, after-school programs, etc.). The A + PAAC approach delivers academic lessons using physical activity, thus there is no reduction in academic instruction time; a desirable feature in the climate of No Child Left Behind of 2001 [45]. A + PAAC is minimal intervention that requires virtually no additional financial resources or time commitment to implement. Classroom teachers can be trained to deliver academic lessons through increased physical activity in the frequently used teacher in-service setting; a cost effective training model.

In summary, this project will evaluate the impact of physically active lessons in the elementary school classroom (A + PAAC) on academic achievement. If successful, the A + PAAC approach could be easily and inexpensively scaled and disseminated across elementary schools in the US using existing personnel and infrastructure to improve both educational quality and health.

## Abbreviations

A + PAAC: Academic achievement and physical activity across the curriculum; PE: Physical education; MVPA: Moderate to vigorous physical activity; WIAT: Weschler individual achievement test; BMI: Body mass index; MET: Metabolic equivalent of task; PACER: Progressive aerobic cardiovascular endurance run; SOFIT: System for observing fitness instruction time.
